#### 3.3.3. Impact of the DFU on QoL

The impact of the DFU on patients’ QoL will be assessed through the Diabetic Foot Ulcer Scale-Short Form (DFS-SF) [42], a self-report questionnaire to be fulfilled by participants to evaluate the effect of the DFU on patients’ general QoL.

#### 3.3.4. Physical and Mental QoL

Patients’ physical and mental health-related QoL will be assessed through the Short-Form Health Survey (SF-36) [43], a self-report questionnaire administered to participants.

### 3.4. Measures of Secondary Outcomes

Data will also be used to assess the following secondary outcomes: perceived stress, psychological morbidity, and DFU representations.

#### 3.4.1. Perceived Stress

The overall stress perceived by patients will be assessed through the Perceived Stress Scale (PSS) [34], a self-reported measure to be answered by participants.

#### 3.4.2. Psychological Morbidity

Psychological morbidity or emotional distress will be assessed through the total score of the Hospital Anxiety and Depression Scale (HADS) [33], comprising both anxiety and depression subscales. HADS is also answered by participants.

#### 3.4.3. DFU Representations

Patient representations regarding the DFU will be evaluated through the Illness Perception Questionnaire—Brief (IPQ-B) [44], a self-report scale administered to participants.

### 3.5. Other Outcome Measures

Health literacy, blood pressure, heart rate, time to complete wound healing, and time to favorable healing prognosis will also be assessed.

#### 3.5.1. Health Literacy

Personal health literacy is evaluated through the Medical Term Recognition Test (METER) [45], a widely used health literacy self-assessment measure administered to participants.

#### 3.5.2. Blood Pressure

Systolic and diastolic pressure, in millimeters of mercury (mmHg), will be assessed through a validated and certified blood pressure measuring device.

#### 3.5.3. Heart Rate

Heart rate, in beats per minute (bpm), will be assessed through a validated and certified blood pressure measuring device.

#### 3.5.4. Time to Complete Wound Healing

This variable corresponds to the time interval (days) between the baseline assessment and the complete DFU healing.

#### 3.5.5. Time to Favorable Healing Prognosis

Based on the wound area, the time to a favorable prognosis will be assessed through the DFU area evolution (reduced versus increased, at the end of the participation in the study, i.e., T1 or T2 assessment moments).

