## Abstract

Diabetic foot ulcer (DFU) is the leading cause of lower-limb amputations, with a significant impact on patients, families, and society. Since DFU medical treatments represent a major socioeconomic burden, cost-effective interventions are needed. This trial aims to assess the effectiveness of a muscle relaxation intervention compared to a hypnosis intervention versus active and passive control groups on DFU healing, physiological indicators of healing prognosis, and quality of life (QoL) in clinically distressed patients with a chronic DFU. A multicenter, randomized controlled trial with three assessment moments (baseline, two months post-intervention, and four months follow-up) will be conducted. Approximately 170 patients will be randomized and allocated to either treatment or control groups. Primary outcomes will be DFU healing, physiological indicators of healing prognosis, and QoL. Secondary outcomes will include perceived stress, psychological morbidity, and DFU representations. The efficacy of sessions on DFU healing will be qualitatively assessed in 12 patients allocated to the treatment and active control groups, as well as their family caregivers. This study will provide evidence regarding the effectiveness of two psychological interventions for the DFU healing process and the QoL of patients, with direct clinical relevance regarding DFU treatment and recurrence.

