## 3. Outcomes and Measures

### 3.1. Participant Timeline

Participants in the intervention and control groups will be assessed at the pre-intervention baseline (T0), at the end of the intervention/two months later at post-test (T1), and six months after T1 at the follow-up (T2). Data will be collected through face-to-face interviews conducted by health psychologists (Researchers 1, 2, and 3). Regarding the biochemical sample collection (biochemical parameter, inflammatory and angiogenic markers, miRNAs, and immune cells), a blood sample will be collected during the consultation at the T0, T1, and T2 assessment moments (Table 1).

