#### 3.3.1. Degree of DFU Healing

Wound healing is defined as the complete epithelization of the wound and is assessed through the RESVECH 2.0-PT [41], a useful and validated tool to monitor the progression of chronic wounds of any etiology through six main parameters: wound area, depth and involved tissues, wound margins, type of tissue in the wound bed, levels of exudates, and presence of signs of infection/inflammations. This questionnaire will be filled out by the participant’s physician or nurse at the end of consultations to monitor DFU progression. Scores range from 0 to 35, where zero indicates complete healing and 35 corresponds to the worse possible wound.

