### 5.2. Data Analysis

The baseline data of the treatments and control groups will be compared using the chi-squared test for binary variables and the independent sample t-test for continuous variables. To prevent overestimating the impact of both interventions, an intention-to-treat approach will be assumed to evaluate the impact on the primary and secondary outcomes. The comparison between the treatment groups versus control groups over time (differences between and within) will be performed through mixed general linear models of analysis of variance for repeated measures. Effect sizes (Cohen’s d coefficient) will also be provided between T0 and T1, T1 and T2, and T0 and T2 to determine if the intervention shows any treatment effect. A significance level of 0.05 will be set for a two-sided test, and the 95% confidence interval will be calculated. In addition, time to complete wound healing and time to favorable healing prognosis (based on the wound size) will be estimated using survival analysis, specifically, single variable and multivariable Cox proportional hazard ratio regression models and Kaplan–Meier plots. All previous analyses will include the DFU stage at the baseline as a control variable. Other confounding clinical factors associated with the outcome variables will also be considered in the statistical analysis.

The data will be analyzed using the Rstudio, R version 3.6.2 (R Core Team, Vienna, Austria) and the SPSS statistics, v. 24.0 (IBM Corp., Armonk, New York, NY, USA).

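### Time to favorable healing prognosis is defined as a wound status without an event date, so the planned Kaplan–Meier and Cox analyses do not fit it

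*Protocol article*

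**What the plan says.** Section 3.5.5 bases the variable on wound area and says that it "will be assessed through the DFU area evolution (reduced versus increased, at the end of the participation in the study", and it identifies the end of participation as "i.e., T1 or T2 assessment moments". It gives no origin, no date of the event, no unit of time and no category for an unchanged area.

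Section 5.2 then states that "time to complete wound healing and time to favorable healing prognosis (based on the wound size) will be estimated using survival analysis", by "single variable and multivariable Cox proportional hazard ratio regression models and Kaplan–Meier plots".

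The neighbouring variable in section 3.5.4, time to complete wound healing, is set out differently. It is "the time interval (days) between the baseline assessment and the complete DFU healing", which supplies origin, event and unit.

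The RESVECH 2.0 score, which includes wound area, is "filled out by the participant’s physician or nurse at the end of consultations to monitor DFU progression" (section 3.3.1). Section 3.5.5 makes no reference to those scores. Section 3.5 places both time variables among the other outcomes, below the primary and secondary tiers.

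**The concern.** A survival model needs a date for each event and a date for each censoring. Section 3.5.5 supplies a yes/no status at the last assessment and nothing else. The outcome and the model are both fixed in the text, and they do not match.

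If the last assessment serves as the event time, two patients with the same reduced wound get different times only because one stopped attending after T1 and the other stayed to T2. An arm with more early leavers would seem to improve faster. An arm that truly improves faster, with the same attendance, would show no advantage. The result would still be reported as a hazard ratio for favorable prognosis and read as a statement about speed.

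**Working it through.** The protocol gives no event count, hazard ratio or power for this variable, so there is no figure to reproduce. The check has three steps.

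**1. What time can the definition yield?**
- *Literal reading:* status at the end of participation. The event time is the time of the last assessment, T1 or T2.
- *Kinder reading:* the first of T1 or T2 at which area is reduced. The event time is again T1 or T2. It means only that the reduction was first seen at that visit, having occurred at some point since the previous one, so it is interval-censored.

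Either way there are two possible values. T1 is at about 2 months. T2 is at month 8 by section 3.1 ("two months later at post-test (T1), and six months after T1 at the follow-up (T2"). It is at month 6 by section 2.2, and by the Abstract ("baseline, two months post-intervention, and four months follow-up") if its four months run from T1. Under the literal reading the same status can thus carry a time 6/2 = 3 or 8/2 = 4 times as long. That ratio describes the time axis and is not a measure of bias. The T2 timing must be reconciled separately.

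**2. Literal reading by hand.** Assume 70% favorable in both arms whatever the exit time, and last assessment at T1 in 30% of one arm and 5% of the other.
- Event proportion at T1: 0.70 × 0.30 = 21.0% versus 0.70 × 0.05 = 3.5%, a ratio of 6.
- Event proportion at T2 among those remaining: 70% versus 70%, a ratio of 1.
- Kaplan–Meier cumulative proportion at T2: 1 − 0.79 × 0.30 = 76.3% versus 1 − 0.965 × 0.30 = 71.1%.

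The arms have identical outcomes, and the whole difference between the curves comes from attendance.

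**3. Simulation.** The group size of 42 is from section 5.1. The rest is assumed: 70% favorable in both arms, exponential times to reduction, the exit shares shown, T1 at day 60, T2 at day 180 or 240. There were 600 runs per scenario, with the log-rank test at two-sided 5% and the median Cox hazard ratio (HR, Efron ties). Monte Carlo error at a 5% rate is √(0.05 × 0.95/600) = 0.9 percentage points. Ranges cover the two T2 dates.

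| Scenario | HR, literal coding | Rejection | HR, true date of reduction | Rejection |
|---|---|---|---|---|
| A: median 20 vs 40 days, exit at T1 11% in both | 0.99–1.00 | 3.7–4.0% | 1.20–1.24 | 11.7–12.3% |
| B: equal speed, exit at T1 30% vs 5% | 1.32–1.33 | 31.7–34.5% | 1.07–1.08 | 5.5–6.5% |
| B2: equal speed, exit at T1 50% vs 10% | 1.60–1.61 | 65.3–65.8% | 1.12–1.13 | 5.0–5.8% |
| C: no difference, exit at T1 11% in both | 0.99–1.01 | 3.7–5.8% | 0.99–1.00 | 4.7–4.8% |

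Literal coding hides a real difference in speed (A) and creates one where none exists (B, B2). It is harmless when exit and speed are equal (C). In B and B2 the true-date HR is slightly above 1 because favorable early leavers are assumed to have improved by the day they left.

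**The case against.** The strongest reply is that no section says the survival time equals time on study. Section 3.5.5 says how the status is classified and is silent on the date, and event-date and censoring rules often sit in a full protocol or analysis plan that is not shown. Dated wound-area scores exist through RESVECH. This stands in part: the time-on-study reading is an inference, and a reader should not conclude that the trial will certainly analyse length of participation. It does not remove the mismatch. The article does not merely omit a date. It ties the variable to T1 or T2, and the kinder reading still gives only two interval-censored values.

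Four stronger readings are tempting, and the documents do not support them:

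- *Healed wounds have no status.* Table 1, footnote a, stops progression scoring once the ulcer has healed. But healing means complete epithelization (section 3.3.1), so the area is reduced by definition, and healing time is recorded (sections 3.2.2 and 3.5.4). Only the unchanged wound has no category.
- *Heavy ties invalidate Cox.* Ties have standard handling, and scenario C shows no inflated error. The loss is in information and interpretation.
- *The hazard ratio will be biased.* That needs exit to differ by arm. The only attrition figure is 11%, for intervention sessions and not split by arm (section 5.1). Section 4.2 describes reminder calls and asks for T2 even when T1 was missed. The Discussion reports poor compliance in the treatment groups, but missed sessions are not the same as leaving the study.
- *The Discussion's aim of timing psychological interventions rests on this variable.* It refers to survival analysis in general, which also covers time to complete healing.

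**Conclusion.** The point holds as a mismatch between an outcome definition and its model. Section 3.5.5 fixes a status without an event date, and section 5.2 treats it as a time to event. Section 3.5.4 shows that the authors state a dated event when they have one, so this is more than condensed wording.

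On the literal reading the hazard ratio is confounded with attendance whenever exit after T1 differs between arms. Under the assumed exit shares of 30% versus 5% and 50% versus 10%, it moves from no effect to about 1.3 and 1.6. Those shares are illustrative and the protocol gives none by arm, so the bias is conditional. On the kinder reading that distortion need not arise for a reduction already seen at T1, but a continuous-time model says nothing about timing beyond the two visits.

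The weight is modest. One outcome in the lowest tier is affected. DFU healing, the physiological indicators and quality of life are not, nor is time to complete healing.

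**What to change.** Choose one of two definitions before analysis and state it in sections 3.5.5 and 5.2.

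1. **Binary outcome (simplest).** Favorable prognosis is an area below baseline at T1 and, separately, at T2. Count a healed ulcer as reduced and an unchanged area as not reduced. Analyse with logistic regression or risk differences, adjusted for baseline DFU stage (already planned in section 5.2) and the stratification factors (hospital, CKD, PAD). Drop the word time from the name.
2. **Dated event, if a time is wanted.** The event is the first consultation at which the RESVECH area item is below its baseline value, with censoring at the last consultation scored. Use an interval-censored model or a discrete-time model with a complementary log-log link.

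Keep Kaplan–Meier and Cox for time to complete wound healing.

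The cost is a redefinition of one outcome and its analysis. The binary version needs no new data and gives up only a timing claim that two visits could hardly support. The dated version requires that the consultation scores and their dates be entered in the database.

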### 2.3. Participant Recruitment and Selection Criteria

Patients with chronic DFU attending the first consultation of the multidisciplinary outpatient clinical of diabetic foot ulcer from three major hospitals in Northern Portugal will be recruited. In the first consultation, researchers (Researchers 1, 2, and 3) will collect the clinical information of each patient to signalize those that meet eligibility criteria. Patients will be consecutively enrolled in the study.

The inclusion criteria are: (i) being 18 years old or more, (ii) having one or two diabetic chronic ulcers (a non-healing ulcer for six or more weeks and less than 12 weeks; in case of patients with two active chronic DFUs, the ulcer with the largest area will be selected as the index ulcer) at the time of baseline assessment, (iii) reporting clinical levels of psychological distress, and iv) providing written informed consent. Clinical distress is assessed according to the Hospital Anxiety and Depression Scale (HADS) [33] and the Perceived Stress Scale (PSS) [34], with patients scoring ≥11 on the HADS subscales or ≥13 (male patients) and ≥17 (female patients) on the PSS evaluated as being clinically distressed.

Exclusion criteria include: (i) the DFU, at the time of baseline assessment, being a relapse; (ii) having three or more DFUs at the time of baseline assessment; (iii) having undergone a transplant; (iv) being on hemodialysis treatment; (v) having a cancer disease; (vi) having degenerative dementia or severe psychiatric illness (e.g., schizophrenia), (vii) receiving psychological counseling, or (viii) taking psychiatric medication during the study period.

For the qualitative study, participants that completed at least 75% of the intervention sessions or placebo sessions (active control group) will be invited to participate, together with their family caregiver. Participants will be purposively selected according to the type of diabetic foot (neuropathic versus neuroischemic) and DFU progression (positive versus negative). The sample will also be selected according to participants’ capacity to provide in-depth and rich-textures information regarding the intervention’s effectiveness since qualitative purposive sampling is considered to be more efficient than random sampling [35]. Thus, the quantitative study sample will include four single-per-participant interviews per group (4 conditions × 3 groups), in a total of 12 patients’ interviews and 12 caregivers’ interviews.

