## 7. Discussions

Given the huge challenge of distress in patients with DFUs, and the limited data evaluating the healing process and QoL of patients with chronic DFUs, the study of the efficacy of two economic stress reduction interventions in clinically distressed patients with chronic DFUs is proposed.

This paper describes the PSY-DFU study protocol, the first national and international multicenter study to address the contribution of psychological variables in DFU healing and QoL. The study also tests the effects of two psychological interventions: individual relaxation and hypnosis, both with guided imagery, on wound healing, physiological indicators of wound healing prognosis, and QoL.

Many complicating factors of diabetes compromise the healing process, making effective treatments challenging. The compliance rate in the treatment groups is one of the major difficulties experienced so far. This is, in part, due to the fact that patients with chronic DFUs often present a long history of medical care, and yet many fail to adhere to the medical treatment and self-management, thus developing negative expectations about psychological interventions. Moreover, in the treatment groups, when DFU is completed healed, the intervention ends, which also contributes to the low-rate compliance. Regarding the DFU progress monitoring, this study would benefit from more advanced and accurate techniques to assess wounds, such as imaging devices. However, none of the three participating hospitals have yet adopted imaging systems to routinely measure DFUs. In addition to the limited strategies to improve adherence to treatments, and the use of more traditional tools to measure chronic DFUs, the non-fully blinded design also represents a limitation of this research.

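### Favourable healing prognosis rests on the direction of wound-area change alone, so a static ulcer that the rule can classify is called favourable about half the time

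*Protocol article*

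**What the plan says.** Section 3.5.5 of the Protocol article bases the outcome on wound area, "assessed through the DFU area evolution (reduced versus increased"), and places the judgement "at the end of the participation in the study, i.e., T1 or T2 assessment moments". It gives no minimum reduction and no class for an unchanged area, and it does not name the value against which a reduction is counted. Baseline is the natural reading, because the companion outcome in section 3.5.4 is the "time interval (days) between the baseline assessment and the complete DFU healing".

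Section 5.2 uses the outcome as an event: "time to favorable healing prognosis (based on the wound size) will be estimated using survival analysis", by Cox models and Kaplan–Meier plots. Section 3.5 places it among the other outcomes, neither primary nor secondary: "time to complete wound healing, and time to favorable healing prognosis will also be assessed".

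On measurement, section 7 (Discussions) states that "none of the three participating hospitals have yet adopted imaging systems to routinely measure DFUs" and that "this study would benefit from more advanced and accurate techniques to assess wounds, such as imaging devices". For patients with two ulcers, section 2.3 says "the ulcer with the largest area will be selected as the index ulcer". Footnote a to Table 1 says that ulcer progression is not assessed at T1 or T2 once the ulcer has healed.

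**The concern.** A rule that looks only at the sign of the change puts its cut-off exactly where measurement error decides the answer. An ulcer that has not moved will read slightly smaller or slightly larger at the next assessment, and the rule turns that noise into a prognosis. Static ulcers are the ones that a prognosis label should set apart, yet they are split between the two classes by chance. An area recorded as equal to baseline has no class at all.

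This is not a detail left to an analysis plan. The article prints the rule, and a later document that added a threshold would be changing the stated definition. At stake is what one of the two survival outcomes means. The primary outcomes are not touched. The point concerns the threshold, not how the event is dated.

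**Working it through.** The documents give no figure for this outcome, so there is nothing to reproduce first.

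**1. Static ulcer, one deciding assessment.** Baseline and later readings of an unchanged ulcer, taken by the same method, are exchangeable. Hence P(later < baseline) = (1 − P(tie))/2. Without ties this is 0.50 for any error distribution. Simulation of 1,000,000 ulcers with log-normal error gave 0.500 at every assumed coefficient of variation (CV) from 5% to 30%.

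**2. A reduction at either T1 or T2 counts.** The ulcer escapes the label only if baseline is the smallest of three exchangeable readings, which has probability 1/3. So P = 1 − 1/3 = 0.667 (simulated 0.667). A reduction at both T1 and T2 needs baseline to be the largest, so P = 1/3.

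**3. Coarse recording.** This assumes log-normal areas with median 3 cm² and log-scale SD 1.

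| Rounding | CV | Ties | Called favourable |
|---|---|---|---|
| 0.1 cm² | 10% | 14.1% | (1 − 0.141)/2 = 43% |
| 0.1 cm² | 20% | 7.6% | (1 − 0.076)/2 = 46% |
| 0.5 cm² | 10% | 44.9% | (1 − 0.449)/2 = 28% |
| 0.5 cm² | 20% | 29.3% | (1 − 0.293)/2 = 35% |

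The share falls only because ties appear, and the rule has no place for ties. Among the ulcers it can classify, the split stays 50:50.

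**4. What a minimum reduction would do.** With log-scale error SD σ = √ln(1 + CV²), a static ulcer appears to shrink by at least a fraction c with probability Φ(ln(1 − c)/(σ√2)). At CV 20%, σ = 0.198 and σ√2 = 0.280. For c = 0.5 this gives Φ(−0.693/0.280) = 0.7%.

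| Required reduction | CV 10% | CV 20% | CV 30% |
|---|---|---|---|
| Any | 50% | 50% | 50% |
| ≥20% | 5.7% | 21.3% | 29.5% |
| ≥30% | 0.6% | 10.2% | 19.5% |
| ≥50% | about 0% | 0.7% | 4.7% |

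The CVs are assumptions. The first row does not depend on them; the others do. In the same way, an ulcer that truly grew by 10% is still called favourable with probability Φ(−ln 1.1/(σ√2)) = 25%, 37% and 41%.

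**5. Does the rule dilute a difference between arms?** This illustration assumes a 0.5 shift in mean log-area change, between-patient SD 1, CV 20%, and 38 per arm (152/4 from section 5.1). The SD of observed change is √(1 + 2 × 0.2²) = 1.039. Power is for a two-proportion test at two-sided 5%.

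| Mean log change, by arm | Any decrease | Power | ≥50% reduction | Power |
|---|---|---|---|---|
| −1.0 v −1.5 | 83.2% v 92.6% | 24% | 61.6% v 78.1% | 35% |
| −0.2 v −0.7 | 57.6% v 75.0% | 36% | 31.8% v 50.3% | 37% |
| 0 v −0.5 | 50.0% v 68.5% | 37% | 25.2% v 42.6% | 36% |

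With no measurement error, the first row under any decrease is 84.1% v 93.3%, almost the same. The weak contrast there comes from the assumed means, which put the rule near its ceiling, and not from error. The 50% cut-off helps only when most ulcers shrink. Analysing log change itself gives Φ(0.5/(1.039 × √(2/38)) − 1.96) = 55% in every row. That comparison contains no healed ulcers, whose log area is undefined.

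**The case against.** The strongest reply is that the effect on the trial is unknown and may be small. This stands. The documents give neither the measurement error nor the proportion of ulcers that stay static. If most ulcers shrink, the coin-flip applies to few patients.

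A reader might infer four stronger conclusions, none of which the documents support:

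- **The reported favourable proportion is too high.** In the first scenario of step 5, error lowers it, from 84.1% to 83.2%.
- **Most ulcers will shrink under standard care, so the outcome sits at its ceiling.** The article does not say so, and section 2.3 enrols ulcers that have already failed to heal for six to under 12 weeks.
- **The rule costs power through measurement error.** Step 5 shows that it hardly does.
- **Choosing the larger of two ulcers as the index makes a spurious decrease likelier.** The direction is right, but the extreme value of 2/3 (one minus the 1/3 chance that the later reading is the largest of three) needs two truly equal ulcers. The share of two-ulcer patients is not given.

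It is also fair that this is an other outcome, that section 7 discloses the measurement limitation, and that the baseline reference and the either-visit reading are inferences. None of this rescues a rule that leaves unchanged areas unclassified and assigns the remaining static ulcers by chance.

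**Conclusion.** The rule is badly fixed. As written, a truly static ulcer that can be classified is called favourable 50% of the time at one assessment, whatever the measurement error, and 67% if either T1 or T2 suffices. Coarse recording lowers the overall share to 28–46% under the assumptions in step 3, by producing ties that the rule cannot place. These figures assume the same measuring method at each visit and baseline as the reference.

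The conclusion is limited to this: the label does not separate static from improving ulcers. No trial-wide misclassification rate or loss of power can be derived from the documents, and the primary and secondary outcomes are not directly affected.

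**What to change.** Name baseline (T0) as the reference. Then choose one of two routes.

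- **Preferred:** analyse the change in index-ulcer area from T0 to T1 and T2 without dichotomising, using a method that accommodates healed ulcers at area zero, such as percentage change or ranks.
- **If a binary or time-to-event version is kept:** require a prespecified minimum percentage reduction above measurement error. Count healed ulcers as favourable, and unchanged ulcers or smaller decreases as not favourable. Healed ulcers need an explicit class because Table 1 stops assessing progression once the ulcer has healed.

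Require a confirming reading only if areas are in fact recorded between T0, T1 and T2. Section 3.3.1 has a wound score with area as one component completed at consultations, but does not say that a measured area is kept, and Table 1 schedules ulcer evolution only at T0, T1 and T2.

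The cost is a change of definition, using areas that the stated rule already needs. A threshold will lower the favourable proportion and must be justified. A 50% cut-off should not be adopted in the expectation of more power, since it gains power only when most ulcers shrink.
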